## Abstract

**Introduction:**

To effectively tackle antibiotic resistance (ABR) a One Health approach is required, focusing on the human, animal and environmental sectors together, and that public education and engagement programs must be part of the overall approach. However, there has been limited research on such programs in low−/middle-income countries (LMICs). Here we describe our plans to evaluate a community-engagement program, known as the community dialogue approach, that takes a One Health approach to tackling ABR in rural communities in Bangladesh, and involves community-led and community-based education and discussion forums. Members of our team previously developed this approach and used it to address other health issues in other LMIC contexts, while our team has previously adapted it for this topic and setting.

**Methods:**

We will use a pragmatic, non-blinded, two-arm, parallel-group, cluster-randomized, controlled trial to primarily evaluate whether the intervention can improve (1) the level of correct and appropriate knowledge about antibiotics, ABR, and antibiotic usage from a One Health perspective, (2) levels of awareness about the existence of antibiotics and ABR, and (3) the relative frequency of self-reported and observable indicators of best practices related to antibiotic usage. Within Cumilla district, we will randomize 50 clusters of villages in a 1:1 ratio. In intervention community clusters trained community volunteers will deliver a set of 11 health education and discussion forums across a 12-month period, while control community clusters will receive no inputs. We will collect outcomes at baseline (pre-randomization) and endline (following the final community dialogue) via two repeated cross-sectional household surveys (each aiming to survey 2,200 participants across all clusters). We will also conduct nested process evaluation and costing studies.

**Discussion:**

Community engagement approaches have successfully addressed other health issues in low resource settings, but there is limited evidence on using community engagement approaches to address ABR in low resource contexts, particularly in Bangladesh. We will closely involve the Bangladeshi health system in this research to ensure feasibility and facilitate scale-up via an embedded approach.

**Clinical trial registration:**

https://doi.org/10.1186/ISRCTN93756764, identifier ISRCTN93756764.

## Introduction

### Background and rationale

Antimicrobial resistance (AMR) is now widely considered to be one of the most important global challenges to public health and development (1). Accurate yearly estimates of global mortality due to antimicrobial resistant infections are not available, but one recent attempt estimated that 4.95 million deaths were associated with bacterial AMR in 2019 (2). Similarly, while highly speculative, a recent estimate under a “low-AMR scenario” predicted annual global costs of $1 trillion annually due to the impacts of AMR from 2030, increasing to $2 trillion annually by 2050 (3). Global efforts to tackle AMR have increasingly emphasized the need to take a One Health approach: recognizing that human, animal and environmental health are all interconnected, and that to successfully tackle AMR we must address the different but interlinked causes of AMR operating within these sectors simultaneously. This is reflected in the 2016 United Nations Political Declaration on AMR (1) and other international action plans, such as the World Health Organization’s (WHO) 2015 Global Action Plan on Antimicrobial Resistance (4).

Low- and middle-income countries (LMICs) are already being more severely impacted by the effects of AMR compared to high-income countries, and this situation is only expected to worsen in the future (2). However, it is not currently possible to robustly identify the different possible causal factors and their relative contributions to the various negative impacts of AMR, given the scale and complexity of the issue. Within LMICs among the factors most often proposed as likely key causes of rising levels of AMR are the sometimes high levels of antimicrobial misuse that occur when treating human and animal health issues (i.e., the prescription or sale of inappropriate and/or unneeded antimicrobials), and in the case of animal husbandry the increasing use of antimicrobials as prophylactics and growth promoters (as has been routinely the case in high income countries for many decades) (5–7). In some LMICs this misuse is facilitated by the easy and unregulated public access to antimicrobials (8), a lack of education and awareness about AMR and its negative impacts (9), and unhelpful cultural beliefs and practices related to medicines and their use (5, 6). Practically speaking, these issues are most problematic in relation to antibiotics, given that most antimicrobials used are antibiotics.

Among all the WHO regions, the risk of AMR infections is estimated to be highest in Southeast Asia (10). In Bangladesh, where this study is based, inappropriate practices in relation to the sale and use of antibiotics are widespread. For example, rural pharmacies appear to routinely sell antibiotics without requiring a prescription, despite this being illegal, and antibiotics are often illegally available from unregulated local shops selling medicines (11, 12). In rural areas public knowledge about antibiotics has been found lacking, while negative attitudes about the need to follow usage guidelines for antibiotics exist, and inappropriate practices reported (13). In rural communities where this study is based only half of adults even report being aware of antibiotics’ existence as a type of medicine (14), while among those adults who do claim to be aware of antibiotics and who report previously using them around 50% report having used them for a cough/cold (14), which are typically self-limiting, viral infections for which antibiotics are not appropriate (15). There is much less evidence on AMR and antimicrobial misuse in relation to small-scale, household-based livestock farming, but the little evidence that exists indicates that individuals frequently use antibiotics inappropriately as prophylactics and growth promoters for their animals, and that they access/purchase antibiotics for their animals when they are ill from informal drug shops (14, 16). Similarly, little research has looked at the environmental aspects of AMR from a community perspective in Bangladesh, but as with many LMICs unsafe practices related to infectious waste (e.g., feces) management are common (17), and studies have shown antibiotic resistant bacteria are frequently present in the environment in communities (18).

The WHO’s 2015 Global Action Plan on Antimicrobial Resistance includes as its first objective (of five) an objective to “Improve awareness and understanding of antimicrobial resistance through effective communication, education and training” (4). This explicitly covers communication and education of the public, as well as professionals. Similarly, Bangladesh’s National Action Plan: Antimicrobial Resistance Containment in Bangladesh 2021–2026 recommends that public communication and education about AMR is prioritized (this document is not publicly available at the time of writing, but members of our research team have access to it). However, it is critically important to go beyond simply raising public awareness of AMR and to actively engage with communities through community engagement approaches, to enable them to identify, develop and implement community-led and contextually-relevant, sustainable solutions (19, 20).

One proposed framework for community engagement emphasizes a high level of community participation, in which equitable partnerships are formed with community members and stakeholders, allowing them to identify, develop, and implement community-led sustainable solutions to issues affecting them and the wider global community, using existing or available resources (21). Based on these principles, an adaptable approach to community engagement was previously developed within rural communities in LMICs by the health research organization Malaria Consortium^1^, known as the community dialogue approach (CDA) (22–24). The goal of the CDA is to train “community-based volunteers … to facilitate regular community forums (referred to as community dialogues) where specific health issues affecting the community are explored, local solutions are identified, and participants collectively decide and plan how best to address the issue.” See *Intervention* below for more details.

Many studies have now looked at how community engagement approaches may address a range of health issues (e.g., (25, 26)). However, there has been relatively little focus on how effective they may be at addressing the drivers of AMR in community settings, with no such studies having been done in the Bangladeshi context that we are aware of. Previously, members of this research team, along with other colleagues, adapted the CDA to the rural Bangladeshi context to address AMR from a One Health perspective. This meant adapting the CDA to focus on community-level and individual-level behaviors and practices related to humans (e.g., sharing of antibiotics), animals (e.g., use of antibiotics to promote growth) and the environment (e.g., inappropriate disposal of antibiotics) that can cause/spread antimicrobial resistant microbes (27–29). This wider research team has also conducted extensive formative research on this intervention within this context using a range of mixed methods, including piloting and evaluating aspects of it on a small scale, establishing its acceptability and the feasibility of delivering it within this context (27–29).

Therefore, in this study we will evaluate this adapted CDA intervention, focusing on AMR from a One Health perspective, within rural Bangladeshi communities, on a large geographical scale, using a robust, pragmatic, randomized, controlled trial design, with associated process evaluation and costing studies. This will provide a comprehensive evaluation, under real-world conditions, of the effectiveness of the intervention and other key aspects of its functioning that are necessary to inform decisions around whether and how to scale the intervention up. Throughout the previous development of the intervention we have worked in an embedded way in collaboration with Bangladeshi government stakeholders (30), including policy makers and senior non-political members of relevant government departments, and we will continue to do so in this evaluation stage of the project. This embedded approach has been (and will continue to be) led by the Bangladeshi members of the research team, who lead/work for ARK Foundation (an independent health research organization)^2^ and the Faculty of Veterinary Medicine at Chattogram Veterinary and Animal Sciences University. This embedded approach will increase the likelihood that the resulting evidence will be used, and it will facilitate scale-up and sustainability of the intervention within the routine Bangladeshi health system, should the evidence support this decision.

This protocol was designed and reported in-line with the Standard Protocol Items: Recommendations for Interventional Trials (SPIRIT) guidelines (31). A completed SPIRIT checklist for this protocol is included (see Supplementary file 1).

### Objectives

Our first and main objective is to use the trial to evaluate whether our 12-month CDA intervention, focused on AMR from a One Health perspective, can improve levels of correct and appropriate knowledge about antibiotics, antibiotic use, and antibiotic resistance (ABR) from a One Health perspective, among adult community members within rural Bangladesh, as measured by our two primary outcomes. Our second objective is to use the trial to explore whether the CDA intervention may improve awareness of antibiotics, awareness of ABR, the presence of appropriate handwashing facilities in households, not sharing of antibiotics with family and friends, not using of antibiotics by individuals or their children for common, typically-viral, acute illnesses, not sharing household water sources with animals, and awareness of the risks of using antibiotic-containing feed for animals, as measured by our secondary outcomes. Our third objective is to carry out a process evaluation of the trial and intervention, using mixed methods and following the UK Medical Research Council’s guidance on developing and evaluating complex interventions, to help us interpret the results of the trial more comprehensively and effectively (32). Our fourth objective is to carry out a costing study of the intervention. Both objective three and four are primarily aimed at enhancing how we can use the results to inform considerations around future scale-up of the intervention.

### Trial design and key details

We will evaluate our intervention using a pragmatic, non-blinded, two-arm, parallel-group, cluster-randomized, controlled, superiority trial, with a repeated cross-sectional data collection design. Full details of the trial methods are below. In summary though, we will randomly allocate clusters, consisting of groups of rural communities (i.e., villages), to either an intervention or control group in a 1:1 ratio (with the randomization stratified by subdistrict). Within intervention clusters volunteer community members will be trained to facilitate a series of 11 distinct educational and discussion forums in each community (each repeated twice and delivered separately to female and male community members), over a period of 12 months, that aim to help their communities understand community-level and individual-level issues related to AMR from a One Health perspective and facilitate decision making around ways to tackle those issues. Control clusters will receive no trial related inputs other than the data collection activities required to collect the trial outcomes and other necessary trial data. We chose a cluster trial design as it is clearly not feasible to randomize delivery of the community education and discussion sessions at an individual level.

We will collect outcomes and other trial data from community members at baseline (pre-randomization) via a household survey. Following the intervention period we will then carry out an endline household survey of community members who were not included in the baseline survey. We will take this repeated cross-sectional approach (rather than a longitudinal approach) for two reasons. First, and most importantly, the baseline data collection will involve an extensive survey on reported knowledge and practices, and this data will be used to create our primary outcomes. We were therefore concerned that the baseline survey itself would have an impact on the effect of the intervention, at least in terms of the knowledge-related primary outcomes, by priming individuals about these issues. Therefore, to avoid contaminating the estimated treatment effect, particularly on the primary outcomes, we decided to ensure we would not follow-up the same individuals as we did at baseline. However, we recognize there may still be some impact of the baseline in this way through impacts diffusing at the community level. Second, we believe it would be challenging to follow-up the same individuals 12 months later and would likely result in quite a lot of missing data.

## Methods

### Study setting

This community-based study will be carried out within Cumilla district, south-east Bangladesh, about 100 km south-east of the capital Dhaka. According to the 2022 census (33) Cumilla has a population of 6,212,216 million. Among these individuals 53.3% are female and 46.7% male, 79.6% live in areas classed as rural and 20.4% live in areas classed as urban, and 76.5% of those aged 7 or older are classed as literate (75.7% of women and 77.5% of men). The district contains 17 subdistricts, known as upazilas, and 3,687 villages. The study will be based in five adjacent, primarily rural, subdistricts: Barura, Brahman Para, Burichang, Daudkandi, and Homna. These subdistricts were purposively selected for three reasons. First, based on the most recent census data (albeit from 2011) on literacy levels (among individuals aged 7+), these five subdistricts have literacy levels that are representative of the full range of subdistrict-level literacy levels found across all Cumilla’s subdistricts (see Supplementary Table S1 in Supplementary file 2). Second, the subdistricts were selected to be adjacent to each other to minimize costs and facilitate ease of access for the Bangladeshi research team (ARK Foundation (34)). Third, the Bangladeshi research team have prior experience of working within these subdistricts on community-based health research.

### Target population

The target population to whom we aim to make inferences are the adult (≥18 years) component of rural communities (i.e., villages) in Bangladesh.

### Cluster description and eligibility criteria

We pragmatically define our clusters as the adult (≥18 years) populations living within the catchment areas of community clinics (CCs). CCs are government-run, community health facilities that provide basic, primary healthcare services to rural communities across the whole of Bangladesh. CC population catchment areas typically cover several villages, usually containing around 6,000 individuals in total but with quite large variations. In our study subdistricts 76% of CC catchment areas covered 2 to 6 villages, while 24% covered 7 to 11 villages (median = 4). In a CC catchment area one village contains the CC building, which is typically a very basic and small structure. The services available at each CC are provided by one community healthcare provider. Community healthcare providers are classed as paramedics and are trained to provide basic healthcare, focusing on maternal and child healthcare, and when to refer patients up to higher levels of public healthcare. See *Community clinics: additional details* in for more details.

The CDA intervention will involve running a series of community-led health education and discussion forums separately within all the villages in each cluster. These forums will be delivered and facilitated by trained volunteer community members that we call facilitators. These facilitators will be supervised by either the community healthcare provider from the CC that covers the community in which they will deliver and facilitate the forums, or by their local health assistant or assistant health inspector (see Supplementary Table S4 in Supplementary file 2). Therefore, the catchment areas of CCs were chosen as a natural unit of clustering for the trial and intervention implementation.

To maximize the generalisability of the results to the target population all CC catchment areas within the study area will be eligible for inclusion in the trial.

### Participant description and eligibility criteria

To maximize generalisability to the target population the eligibility criteria for participants are also minimal, but they differ slightly between the baseline and endline surveys. For the baseline survey individuals will be eligible if they are aged ≥18 and have lived within the community that they are being sampled from for the past 12 months without having lived elsewhere for more than a month. However, for the endline survey individuals will be eligible if they meet the same criteria but they must also not have been a participant in the baseline survey, as explained in the *Trial design and key details* section.

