#### Presence of appropriate handwashing facilities in the household

A binary indicator of whether there was a handwashing facility in the participant’s household with water and either soap, alcohol gel, or detergent (either ash, mud or sand) or not. This was determined via visual inspection by the data collectors. This outcome is to allow us to explore whether the CDs may increase the relative frequency of the presence of appropriate handwashing facilities within households, which is one focal issue in the CDs.

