#### Sharing of water sources with animals

This outcome only applies to the subgroup of individuals in the sample who report that their household owns any animals. It is a binary indicator of whether animals can access and drink from the same source of water used by the participant’s household to drink and cook with. This was determined via visual inspection by the data collectors. This outcome is to allow us to explore whether the CDs may decease the relative frequency of such water sharing within households, which is one focal issue in the CDs.

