They will then sample and interview the first available eligible individual at this household who is of the opposite sex to the first participant. This sex switching will then be repeated for each subsequent participant. This is to maintain an approximate 1:1 sex ratio. Although the sex ratio in the population being sampled should be approximately equal without this process we may end up with a moderate to large sex imbalance depending on the availability of females vs. males during the surveys. They will then repeat this household skipping selection process, while avoiding households they have previously sampled, until they have selected the required number of participants for that village.

If an eligible individual declines to participate then they will try and recruit another eligible individual in that household or move onto the next nearest household. This approach clearly does not mitigate against sampling bias due to differential participation, and this may affect the generalisability of the results, but it does maintain the target sample size and power. Where it is not possible to sample 22 or 44 individuals from separate households based on the household skip pattern, due to a lack of households, they will modify the skip pattern accordingly.

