#### Data collection team

All data will be collected by two field teams, one created for the baseline survey and one created for the endline survey. Each team will consist of five or six enumerators (depending on how efficient the baseline team is), who will be chosen based on having experience of collecting data health survey data in these settings using tablets (we expect these individuals to be largely/entirely made-up of MSc students from Dhaka University studying health related degrees). The team will undergo a 5-day training program, delivered by members of the Bangladeshi research team and a member of the data collection app team. The training will cover the goals of the study, its design, the survey locations, the household and participant sampling methods, the questionnaire and data collection processes.

We will check their understanding and ability to collect data using a mock test on the survey questionnaire. This will allow us to address any weaknesses in their performance and any final issues identified with delivering the questionnaire. They will then practice sampling households and collecting data from a small number of community members in a similar field setting to the study sites, but in a site that will not form part of the study. There will then be a final day where the data collectors can discuss their learning from the practice field trip and solve any remaining issues.

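### The endline criterion excludes the baseline interviewee but not that person's household, leaving open the nearest route for survey priming

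*Protocol article*

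**What the plan says.** The section Trial design and key details explains why different people are surveyed at the two time points. The main worry is that the long baseline questionnaire could alter the effect of the intervention, "at least in terms of the knowledge-related primary outcomes, by priming individuals about these issues". The authors conclude: "we decided to ensure we would not follow-up the same individuals as we did at baseline". They add that some effect of the baseline survey may still spread at community level.

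The rule that carries this out is in Participant description and eligibility criteria. Endline participants meet the baseline criteria and, in addition, "they must also not have been a participant in the baseline survey". The design section words it the same way: "we will then carry out an endline household survey of community members who were not included in the baseline survey". Both act on the individual.

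Households appear in Participant sampling, where the data collectors repeat the skip pattern "while avoiding households they have previously sampled". That clause is part of the walk that fills one village's quota. Data collection team provides for two field teams, "one created for the baseline survey and one created for the endline survey". The surveyed villages are fixed by rule: the village with the community clinic and the next nearest one, with 22 participants each.

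**The concern.** Interviews are held at the household, with one participant in each. If the baseline interview primes anyone besides the interviewee, the other adults in that home are the most obvious candidates, yet they remain eligible at endline. The household-avoidance clause reads as applying within one survey round, and a separately created endline team has no stated way of knowing which homes were visited before.

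What is at stake is the purpose behind the repeated cross-sectional design. The authors gave up individual follow-up mainly so that the survey would not contaminate the estimated effect on the knowledge scores. If priming makes the dialogues more or less effective for those exposed to it, re-entering baseline households brings some of that back into the endline contrast. The community-level diffusion that the authors concede is more remote than diffusion within a home, and an eligibility rule can remove the household part.

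**Working it through.** The protocol gives no figure for household overlap, so there is none to reproduce. The check has three steps.

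**1. Do the passages leave the household open?** The eligibility section and the design section exclude a person. The avoidance clause in Participant sampling ends when the village quota is met, so its natural reach is one round. Villages are chosen by a fixed rule, so both rounds return to the same ones. No section excludes a baseline household at endline.

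**2. How often would a baseline household be drawn again?**

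Inputs from the protocol:
- about 6,000 people per cluster, and 2 to 11 villages with a median of 4 (Cluster description and eligibility criteria)
- 22 participants per village per round (Participant sampling)

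Assumption: 4 to 5 people per household, which the document does not give.

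Households per village: H = 6,000 / villages / household size. If selection in the two rounds is independent and random, the expected share of endline interviews in a baseline household is f = 22 / H.

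| Villages per cluster | H (size 4; size 5) | f | Interviews out of 2,200 if all clusters were like this |
|---|---|---|---|
| 2 | 750; 600 | 2.9%; 3.7% | 65; 81 |
| 4 (median) | 375; 300 | 5.9%; 7.3% | 129; 161 |
| 6 | 250; 200 | 8.8%; 11.0% | 194; 242 |
| 11 | 136; 109 | 16.1%; 20.2% | 355; 444 |

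Two things move f in opposite directions. The sampling walk starts from the village centre in both rounds and moves between neighbouring homes, so overlap should exceed the random figure. Simulating the walk twice on a uniform layout of 333 households (6,000 / 4 / 4.5) gives a mean of roughly 11% to 21%, depending on how passed and revisited homes are handled, against 22/333 = 6.6% at random. The real layout is unknown, so this range shows direction more than size. Against that, a redrawn household counts only if a second eligible adult of the sex then required is available.

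**3. What would this do to the treatment effect?** Let p1 and p0 be the average priming effect on the score of a co-resident in the intervention and control arms. The endline contrast is then the unprimed contrast plus f × (p1 − p0). The baseline survey precedes randomization and runs the same way in both arms, so equal priming (p1 = p0) cancels. Only the interaction d = p1 − p0 remains. With d assumed to be 5 to 10 points:
- median village, random overlap: 0.059 × 5 = 0.3 to 0.073 × 10 = 0.7 points
- 11 villages per cluster: 0.161 × 5 = 0.8 to 0.202 × 10 = 2.0 points
- median village with the simulated walk: 0.11 × 5 = 0.6 to 0.21 × 10 = 2.1 points, before removing homes with no second eligible adult

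The Sample size section targets a difference of 15 points.

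**The case against.** A reader might infer that the criterion contradicts the design's stated aim. It does not. The literal aim is not to follow up the same individuals, and the rule does exactly that. The authors also considered spread beyond the interviewee and disclosed it, and talk within a home could be counted as part of that. This part of the objection stands. What remains is that the aim serves a wider purpose, an uncontaminated treatment effect, which a person-level rule meets only in part.

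A reader might also infer a breach for the household-level outcomes. For handwashing facilities the protocol says "This was determined via visual inspection by the data collectors", and the water outcome records "whether animals can access and drink from the same source of water", so the same facility could be inspected in both rounds. The documents do not support calling that a design breach. Repeated cross-sections need not use disjoint households, seeing a facility twice does not bias an endline comparison between arms, the stated worry is priming mainly on the primary outcomes, and these are exploratory secondary outcomes.

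Third, the size is soft. Nothing says that other adults hear the baseline interview or learn correct answers from it. An interaction of 5 to 10 points is one third to two thirds of the 15-point target, assigned to people who were not interviewed, and it would have to last through the 12-month programme. The 2-point values need either the smallest villages throughout, although 76% of catchments have 2 to 6 villages, or the most clustered walk together with the largest interaction. All of this stands and keeps the point minor.

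Finally, field screening detail may sit in the questionnaire supplement, which is not shown. The eligibility criterion itself, however, is stated in the article, and at person level.

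**Conclusion.** The gap is real but modest. The endline criterion and the sampling text leave other adults of baseline households eligible in the same villages, and this is the nearest remaining route for the priming that the design seeks to keep out. It is an incomplete safeguard, and the text does not contradict itself.

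On random overlap with an assumed household size of 4 to 5, about 6% to 7% of endline interviews are involved at the median village size, and about 3% to 20% over the stated range of villages. The centre-based walk raises this by an amount that depends on layout; the need for a second eligible adult lowers it. Bias arises only through a priming-by-intervention interaction. At the median random overlap it stays under about 1 point for an assumed 5 to 10 points. Both the interaction and the exposure of co-residents are assumptions. The case for acting is that the remedy is cheap and serves the authors' own main reason for the design.

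**What to change.** Change the endline criterion so that adults are ineligible if they live in a household where anyone took part in the baseline survey. Apply it with one question at the door, and move to the next nearest household if the answer is yes. In very small villages where this would exhaust the households, relax the rule and record where that was done. State also whether the avoidance clause in Participant sampling applies within a round or across rounds.

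The cost is one sentence, one question and about 22 fewer eligible households per village: 6% to 7% of households at the median village size, up to about 20% at 11 villages per cluster, on the same assumptions. Sample size is unchanged.

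Trial status expects endline data by 31/5/2024, so the interviews may already be done. In that case, if baseline households can be identified, repeat the primary analyses without them as a sensitivity analysis. The article names cluster and village codes but no household identifier, so this may not be possible. If it is not, name the household route as a limitation alongside the community-level diffusion already acknowledged.
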